### Secondary objectives

To measure the present level of implementation of ACP in all participating hospital units.To evaluate whether the implementation support, relative to no support, is associated with improved implementation of ACP, measured with the ACP fidelity scale (sum score, the quality subscale, the implementation subscale and the penetration rate subscale).To identify barriers to, facilitators for and experiences with implementing ACP among the stakeholders at the a) clinical, b) health care service- and c) municipal, regional and national level.To explore moral dilemmas and conflicting interests related to ACP, and strategies on how to resolve them.To explore benefits and disadvantages with ACP among patients and their next of kin, and to explore the benefits and disadvantages of both the implementation support and ACP among health care personnel and the implementation teams.To investigate whether the implementation support is associated with improved quality of communication and decision-making when approaching the end of life for patients and next of kin, better congruence between the patient’s preferences for information and involvement and the attending clinician’s perceptions of the same, and improvements of other relevant outcomes for patients, next of kin and the attending clinician.To assess whether higher level of implementation (fidelity) of ACP is associated with improved outcomes for patients, next of kin, the staff and the services.To measure, before and during the implementation process, health care personnel’s perceptions, attitudes, self-efficacy, confidence in, and experiences in relation to information giving and involvement of patients and next of kin.To measure healthcare utilization, costs, and the cost-effectiveness of the implementation and of ACP in the routine health care in hospital units.

## Methods

### Trial design

The project is a multicentre cluster randomized controlled trial (CRCT). Each participating geriatric unit, with responsibility to provide medical care to acutely admitted older medical patients, constitutes one cluster and is the unit of randomization. Figure 1 gives an overview of the study design. The article conforms to the Standard Protocol Items: Recommendations for Interventional Trials (SPIRIT) [36] (Additional file 1), and the study results will reported in accordance with the Consort 2010 extension to cluster randomized trials. All methods carried out in the study will be performed in accordance with relevant guidelines and regulations.

**Fig. 1 Fig1:**
[figure not shown]
The study design of the Norwegian ACP trial

### Setting

Implementation of ACP in the routine health care in Norwegian hospitals is pioneering work, so the geriatric milieu was chosen because of their preexisting focus on and competence in communication, patient involvement and interdisciplinarity in the care for acutely admitted frail older adults. All 14 hospitals in the South-Eastern Norway Regional Health Authority with a geriatric unit or medical wards with geriatric beds were invited to participate in the trial. Of the 14 hospitals, 12 agreed to participate in the trial. All units treat patients from their discrete geographical catchment area, with a total catchment area of 2 372 150 inhabitants, 43% of the total population in Norway. The reason given for non-participation was the lack of capacity to engage in a research project. A full list of the participating units, situated in both urban and more rural areas, is available at ClinicalTrials.com. The difference in size is partly due to differences in the size of the catchment area, and it also reflects the differences within the Regional Health Authority in how geriatric medical services are organized and prioritized.

### Selection, allocation of clusters and sample size

The organization and size of the acute geriatric inpatient care in the included hospitals varied a lot. We selected the units that a) had geriatric doctors and b) were either defined geriatric units, or medical wards with geriatric beds. One exception is one hospital that has a general medicine unit without defined geriatric beds, but with a geriatric doctor and with similar responsibility towards the geriatric patients in their catchment area as the other units. In Norway, many geriatric patients are admitted to various medical wards (cardiology, respiratory medicine, nephrology etc.). The geriatric units and geriatric beds are usually reserved for acutely ill home-dwelling older patients who are expected to benefit from a multidisciplinary geriatric team approach: to evaluate their functional and cognitive status as well as their level of frailty and to develop an individualized plan to preserve function along with treating the acute condition. Three of the units also included beds for stroke patients, and one of the units only had beds defined as "stroke beds". The units with stroke beds were included as a whole if the unit had the main responsibility for geriatric patients in need of acute hospital admittance in their catchment area and were the unit with the highest level of geriatric expertise at the hospital (at least one geriatrician among the staff). The beds in these units were often used interchangeably for geriatric patients and stroke patients depending on the needs.

The units were sorted from one to 12 according to the number of geriatric beds and then stratified into three strata: four clusters with 16 to 23 beds, six clusters with 6 to 10 beds and two clusters with 4 and 5 beds respectively. In each block, the clusters were randomized to either the intervention or the control arm with an allocation ratio of 1:1. An independent professor in epidemiology performed the allocation using the Microsoft Excel RAND-function, only knowing the numbers of the clusters. The randomization was performed to achieve a balance in unit types in the intervention and control arm and a similar size of the two arms including a similar number of admitted patients filling the inclusion criteria. All hospitals are located in cities or towns. The purpose of the stratification was primarily to achieve a balance in the number of patients and next of kin between the two arms, and secondly to include units of various sizes in both.

The study has primary outcomes for the implementation and for the clinical effectiveness. The primary outcome for the implementation outcome sub-study is the differences in fidelity changes between the arms. The unit of analysis for the fidelity scores is the health care units or clusters. Fidelity is rated on 5-point scales (1 = poor fidelity, 5 = high fidelity). Based on previous research (mean difference 1.82 and average SD 0.80 after 18 months with implementation support), we have calculated that we need at least four clusters in each arm to show that implementation support gives a significant increase in fidelity, based on 5% two-tailed significance and 80% power. If the differences are smaller in our study, we will need a larger sample. Due to the possibility of unit drop-out during the project period and to secure sufficient power, we have included six units in the intervention arm and six in the control arm.

The primary outcomes for the clinical effectiveness study “The triadic sub-study with patients, next of kin and clinicians” are described under “outcomes”. The unit of analysis is the individuals recruited in each cluster. Since we have not found comparable studies that have published data on these instruments, we decided to use a 0.5 SD improvement (medium effect) when calculating the sample size. Based on a 0.5 SD increase in the primary outcome and an Intra-class Correlation Coefficient (ICC) of 0.05, we need 132 patients in each arm or 22 per cluster with six clusters in each arm to achieve 80% power to detect a difference in the primary outcome among patients, between groups with a certainty of 95%. Taking into account the possibility of patients in the control arm receiving ACP, and incomplete or missing data, we aim to recruit at least 35 patients per cluster. A similar power calculation with the same conservative assumptions has been done for the primary outcomes for next of kin and clinicians with the same results (35 next of kin and 35 clinicians per cluster).

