#### Data analysis

Demographic and clinical data about the patients will be used to assess whether the patients in the control and intervention units are comparable. In addition, the participating units will collect basic and anonymous clinical information about all patients admitted to the units at shorter random time periods, to get more information about the participant units and to compare the included patients with all admitted patients.

Number and percentages of invitation to and participation in ACP for patients and next of kin will be calculated and compared between intervention and control group. The primary statistical analyses will be the difference in mean outcomes between participants in the intervention and the control group using linear mixed effects models. The random part of the model will consist of random intercept for patient or relative identification nested within centre. Missing data will be handled by multiple imputation using predictive means matching with 100 imputed data sets.

If the analyses show differences in the intervention and control arm, we will perform analyses to assess if higher fidelity score (higher levels of implementation) is associated with improved outcomes for patients, next of kin, and clinicians. For the secondary outcomes, we will compute average outcomes and SD for the intervention and the control group and use the t-test to determine if there is a significant difference between groups.

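### The sample sizes said to give 80% power fall short once the 12 clusters are allowed for: 22 patients per cluster gives about 72%, 35 is the bare requirement, and four units per arm gives 76% for fidelity

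*Protocol article*

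**What the plan says.** Both calculations are in the protocol article, in the section on selection and allocation of clusters and sample size.

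- **Triadic sub-study.** Having found no comparable published data, the authors write "we decided to use a 0.5 SD improvement (medium effect) when calculating the sample size". They add "an Intra-class Correlation Coefficient (ICC) of 0.05" and conclude "we need 132 patients in each arm or 22 per cluster with six clusters in each arm to achieve 80% power", for a difference "between groups with a certainty of 95"%. The target is then raised: "Taking into account the possibility of patients in the control arm receiving ACP, and incomplete or missing data, we aim to recruit at least 35" per cluster. No rate of loss or contamination is given. The same calculation, called conservative, is said to give the same numbers for next of kin and clinicians.
- **Fidelity.** From a mean difference of 1.82 and an average SD of 0.80, at 5% two-tailed and 80% power, the article states "we need at least four clusters in each arm to show that implementation support gives a significant increase in fidelity". Six per arm were included to allow for drop-out and to secure power.

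On analysis, the fidelity section specifies an independent samples t-test on the change from baseline to 18 months. The data analysis section of the triadic sub-study specifies "the difference in mean outcomes between participants in the intervention and the control group using linear mixed effects models". It does not state how degrees of freedom are obtained.

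**The concern.** In a cluster-randomised comparison the evidence on the arm effect comes from the spread between clusters. With six clusters per arm that spread is estimated on about 10 degrees of freedom, and the two-sided 5% critical value is 2.23, not 1.96. A calculation that multiplies an individually randomised sample size by a design effect ignores this, and with 12 clusters the difference is material.

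If 22 per cluster does not give 80% power, the step from 22 to 35 is not a margin. A reader of the protocol would conclude that up to (35 − 22)/35 = 37% of patients per cluster could be lost with 80% power intact. A null triadic result could then be read as stronger evidence against a 0.5 SD effect than it is. The point affects all the triadic primary outcomes, because one calculation serves patients, next of kin and clinicians.

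The fidelity statement has the same fault on a smaller scale: a minimum of four units per arm leaves 6 degrees of freedom.

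**Working it through.** **Inputs from the protocol.** Effect 0.5 SD; ICC 0.05; k = 6 clusters per arm; 1:1 allocation; 5% significance, taken as two-sided (sidedness is stated only for fidelity). Fidelity: difference 1.82, SD 0.80, 5% two-sided, t-test. I take 0.80 as the SD of change, which the protocol does not specify, and assume equal cluster sizes unless stated.

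**1. Reproducing the plan's figure.** Individually randomised n per arm = 2 × (1.96 + 0.8416)² / 0.5² = 62.8, so 63, or 64 with the individual-level t-test. The design effect at m = 22 is 1 + 21 × 0.05 = 2.05. Then 63 × 2.05 = 129.2 and 64 × 2.05 = 131.2, which rounds up to 132 = 6 × 22. Normal-quantile power at 22 per cluster is 81.0%. The stated figure is therefore reproduced, but only with large-sample quantiles.

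**2. Power with 12 clusters.** SE = √[2(1 + (m − 1) × 0.05) / (6m)]; noncentrality = 0.5/SE; noncentral t on 2 × 6 − 2 = 10 df.

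| Evaluable per cluster | Design effect | SE | Noncentrality | Power | Effect detectable at 80% |
|---|---|---|---|---|---|
| 22 | 2.05 | 0.1762 | 2.837 | 72.5% | 0.55 SD |
| 28 | 2.35 | 0.1673 | 2.989 | 76.9% | 0.52 SD |
| 34 | 2.65 | 0.1612 | 3.102 | 79.8% | 0.50 SD |
| 35 | 2.70 | 0.1604 | 3.118 | 80.2% | 0.50 SD |

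Thirty-five is the first whole number to reach 80%. Simulation of cluster means (400,000 runs) gave 72.5% at 22 and 80.1% at 35.

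**3. Does the unstated df method matter?** In a simulated balanced REML mixed model at 22 per cluster, small-sample df gave 72% to 73% power. Using 1.96 gave 80.1%, but with a two-sided type I error of 7.3% (7.7% at 35 per cluster). So 80% at 22 is not 80% at the 5% level.

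**4. What loss or dilution would do.** The protocol gives no rates, so these are illustrative assumptions:
- 20% not evaluable (28 of 35 per cluster): 76.9%.
- Effect diluted by 10% to 0.45 SD by control-arm ACP, all 35 evaluable: 0.45/0.1604 = 2.806, power 71.6%.
- Both: 0.45/0.1673 = 2.690, power 68.0%.
- Uneven recruitment averaging 35, coefficient of variation 0.55: design effect 1 + [(1 + 0.55²) × 35 − 1] × 0.05 = 3.23, power 72.9%.

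**5. Sensitivity to the ICC.** On 10 df, power at 22 / 28 / 35 per cluster is 77% / 82% / 85% at ICC 0.04 and 82% / 87% / 90% at ICC 0.03.

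**6. Fidelity.** d = 1.82/0.80 = 2.275. The normal formula gives 2 × (2.8016/2.275)² = 3.03, rounded up to 4, which matches the plan. Under the t-test, noncentrality is 2.275 × √(n/2) on 2n − 2 df:

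| Units per arm | df | Noncentrality | Power |
|---|---|---|---|
| 4 | 6 | 3.217 | 76.4% |
| 5 | 8 | 3.597 | 88.2% |
| 6 | 10 | 3.940 | 94.3% |

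**The case against.** The strongest reply is that the trial is not run at the minima. The protocol says "we aim to recruit at least 35 patients per cluster" and includes six units per arm, and at those numbers power is 80.2% and 94.3% even on the stricter basis. That stands. The shortfall belongs to the figures of 22 and four, and to the reading of 35 as a figure with reserve.

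A second reply is that the design-effect formula is standard, so this is not a slip in the sum, and that the df method for the mixed model may be in an analysis plan not shown. The first half is right: the figure reproduces. The second half does not help, because valid small-sample df give about 72% at 22, and large-sample inference breaks the stated 5% level.

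Third, the result depends on an assumed ICC. At 0.04 or below, 35 does hold some reserve, so the statement about reserve must be tied to ICC 0.05, the plan's own value. Fourth, the loss, dilution and unevenness rates are mine. The protocol aims for at least 35 in every cluster, and its Discussion thinks it unlikely that control units will implement ACP, although it accepts that elements are already in use. Those scenarios show direction and scale and are not forecasts. Multiple imputation is planned, so counting only evaluable patients simplifies matters.

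Finally, the fidelity result depends on reading 0.80 as the SD of change; with an SD of 0.76, four per arm would reach 80%.

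**Conclusion.** The concern holds. At the plan's own 0.5 SD and ICC 0.05, with 12 equal clusters and a two-sided 5% test on 10 df, 22 per cluster gives 72.5% power, about 8 points below the claim. The target of 35 is what 80% requires with complete data and no contamination, so it cannot also cover the losses it was set to absorb. Ten df is not a harsh choice: adjusting for the three size strata (8 df, no variance gain assumed) gives 70.1% at 22 and 77.9% at 35.

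The fidelity minimum of four units per arm is also wrong under the specified t-test (76.4%, taking 0.80 as the SD of change). This is of little practical weight, since six units per arm were included and 88% power remains if each arm loses one. The substance of the point is the triadic sub-study. It should be corrected, but it does not undermine the design.

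**What to change.** Keep the 12 units and 420 triads and restate the figures in the sample size section:

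- **Triadic sub-study.** With six clusters per arm, ICC 0.05 and a two-sided 5% test on 10 df, 35 evaluable per cluster gives 80% power for 0.50 SD. At 80% power, 28 evaluable detects 0.52 SD and 22 evaluable detects 0.55 SD. Apply the same restatement to next of kin and clinicians.
- **Reserve.** State that at ICC 0.05 the target of 35 contains no allowance for control-arm ACP or missing data. A line giving power at ICC 0.03 and 0.04 would show how far this depends on the ICC.
- **Fidelity.** Replace the minimum of four units per arm with five, say that 0.80 is taken as the SD of change, and state that six per arm gives 94% and tolerates the loss of one unit per arm.

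The cost is text only, with no extra patients or units. The stated power becomes less favourable.

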### Research methodology

The multicentre trial is both an implementation study and a clinical effectiveness study. Our project includes two complex interventions on a large scale in ordinary services: a clinical intervention (ACP) and an implementation intervention. We will use a responsive evaluation approach [37] in combination with participatory action research, the CRCT design, health economics and empirical ethics. Responsive evaluation is characterised by engagement with all stakeholders, and combining professional, scientific, and experiential knowledge. Furthermore, we want to do multilevel evaluation research also outside the units participating in the CRCT and use process evaluation to provide feedback on the preliminary results to the intervention arm as part of the implementation intervention (formative evaluation). In sum, this requires the use of mixed methods (i.e. quantitative and qualitative research methods) – multidisciplinary approaches, and to include different stakeholders and sub-studies with different primary outcomes.

The project design emphasises strong stakeholder involvement before, during and after the project. The health care personnel, the patients, the next of kin, and the health services will play an important role in the development of effective implementation strategies and optimization of the ACP intervention: as stakeholders, as experts by experience, and through the data collected in the qualitative and quantitative sub-studies. The project plans and results will also be discussed at the annual network meetings of the national ACP network to get input and to inspire other research and innovation.

Our methodological design follows the Medical Research Council’s recommendations on evaluating complex interventions [26] and Proctor et al.’s recommendations on outcomes for implementation research [38]. That is, we include more than one method, both process and outcome research, and formative evaluation, more than one primary outcome and different types of outcomes. This approach makes it possible to monitor and adjust the implementation process and study the effect of ACP-implementation both on the individual and organisational level. In the current project, we will further exploit and develop this fidelity scale to assess the implementation of ACP thoroughly, and to be able to assess and compare the levels of ACP implementation, service outcomes, and outcomes for patients and next of kin.

### Piloting and feasibility of questionnaires and interview guides

Two past large multi-center studies from Centre for medical ethics (CME), “Implementing advance care planning in nursing homes” and “Implementation of guidelines on family involvement for persons with psychotic disorders in community mental health centres (IFIP)-trial” have ensured knowledge and experience with feasibility, implementation and evaluation, and serve as pilots for the current trial [39, 40]. All interview guides and questionnaires are built upon these and other relevant past studies [41–49], and have thus been pretested in implementation, health service, and clinical research focusing on involvement of severely ill patients and their close relatives in different health care contexts. Further tailoring, piloting and testing will be performed among older patients, next of kin and health care personnel in geriatric units, and the questionnaires will be adjusted according to feedback on relevance and feasibility.

### The ACP interventions

The ACP interventions in this study, combining implementation strategies, an implementation intervention and the clinical intervention ACP, were developed by the project group. It is building upon research at CME on end-of-life ethics, patient involvement, decision making processes for older patients and their next of kin and ACP in nursing homes in Norway, and national and international research and guidelines on ACP and end-of-life decision-making.

The ACP interventions consist of the following elements (described in detail in Additional file 2).I Clinical intervention: advance care planning1.1 Routine identification, information and invitation to ACP to all eligible patients and next of kin.1.2 ACP conversations routinely provided to all consenting patients and their next of kin.1.3 Documentation and collaboration with other health care services and levels.II Implementation intervention2.1 Implementation team.2.2 ACP coordinator.2.3 Training and supervision: Kick-off, training of resource persons and health care personnel including practical exercises, monthly contact with units, network meetings.2.4 Toolkit and shared resources: ACP guideline, pocket card, teaching material, information leaflets, documentation templates etc.2.5 Structured fidelity measurements of the implementation level of a) the implementation interventions and b) the clinical intervention, with tailored feedback and supervision.2.6 Evaluation of the intervention and implementation.III Implementation strategies3.1 Ensuring leadership commitment.3.2 Responsive evaluation.3.3 Whole ward approach.3.4 Train the trainer model.3.5 Sustainability after the project.

### The implementation strategies

The hospital units in the intervention arm will receive support through the implementation strategies and implementation interventions for 18 months to be able to use the clinical intervention ACP in routine health care. The control units will provide treatment as usual during this period and receive implementation support after the last fidelity measurement at 18 months.

To secure sustainability, both the evaluation plan and the implementation support emphasise a “whole ward approach” [39]. By this we mean recruiting whole units through the CRCT design (and not only individual patients or next of kin), involvement of all employees, leadership commitment, ACP performed by regular staff, train-the-trainer model, minimal off-site training, freely available ACP-guideline and didactic materials, ACP-invitations to all patients in the units who are able to participate, encouraging next of kins’ participation, and supported decision-making if the patient is cognitively impaired [50]. We have recently used parts of this approach in an ACP-study in nursing homes [39, 51]. Our results demonstrate significant improvement of user and family involvement on entire units, not only for patients offered ACP [52].

The implementation support starts with a kick-off for all units. An initial meeting with all involved parties at each unit is recommended. All participating units will recruit a local coordinator for the project. Furthermore, the intervention units assign an implementation team, consisting of one or more health care professionals and the unit leader, which will ensure the local implementation. The project group will provide, in a train-the-trainer model, training and supervision for these local resource persons. We will encourage the implementation teams to meet 1–2 times monthly in the intervention period, and the project group will have monthly joint meetings with the teams digitally. The results from the detailed fidelity assessments (described below) will be used to provide tailored feedback to each intervention unit three times during the implementation period (formative evaluation). Additionally, during the 18 months of intervention, we will gather the implementation teams across all the intervention units in network meetings every sixth month for networking and discussion. Written notes from these meetings will be included in the qualitative evaluation study (see below).

